### Treatment integrity

The treatment integrity of the PEARL intervention will be ensured by means of (1) reference to the PEARL Treatment Manual, which defines the characteristics and sequencing of the intervention and provides examples of approaches to respond to disruptions or deviations and (2) regular supervision of PEARL therapists by PEARL developers, which will include review of selected video-recorded sessions. Evaluation will be conducted by PEARL developers, using the PEARL Treatment Integrity Scale (see Additional file 1) adapted from CALM treatment integrity tools [8].

### Outcomes

#### Feasibility

Feasibility will be evaluated in terms of recruitment, retention, and adherence. Recruitment will be assessed by capturing the number of patients who consent to participate after referral and screening. Retention will be assessed by tracking completion of study measures across all time points. Adherence will be assessed by tracking the number of PEARL sessions completed.

#### Acceptability

Participants will be interviewed regarding their experiences with PEARL, including acceptability, and perceived positive and negative effects of the intervention, with a semi-structured interview guide (see Additional file 2). Interviews will be video recorded and professionally transcribed.

#### Safety

This study will utilize the Common Terminology Criteria for Adverse Events (CTCAE) version 5.0 [37] for toxicity and adverse event (AE) reporting. AEs attributed to psilocybin will be monitored for and recorded after the psilocybin session. During the psilocybin session, the Monitor Rating Questionnaire, adapted from the measure used by Griffiths et al. [18], will be completed by therapists to capture AEs including elevated heart rate and blood pressure, confusion, headache, nausea/vomiting, anxiety, and paranoia. Cardiovascular variables (heart rate and blood pressure) will be measured during the dosing session at the following time points: baseline, 30, 90, 150, 210, 270, and 330 min post-dose administration and at the end of the session with a ± 15 min window. Vital signs will be measured more frequently if there are abnormal readings of heart rate and blood pressure, or if there is chest pain, shortness of breath, neurological symptoms, or any other signs or symptoms that may be indicative of a medical complication.

Serious adverse events (SAEs) will be tracked until study completion and will be defined as any adverse drug experience that results in death, is life-threatening, requires hospital admission, results in persistent or significant disability, or may jeopardize the participant or necessitate medical intervention to prevent one of the aforementioned events.

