### Objectives

1.a. To assess the feasibility of PEARL therapy with attention to recruitment, retention, and adherence.1.b. To assess the acceptability of PEARL therapy from the perspective of patients.1.c. To assess the safety of PEARL therapy.2.a. To explore the preliminary efficacy of PEARL regarding outcomes including death-related distress, depressive symptoms, anxiety, demoralization, spiritual wellbeing, quality of life, and desire for hastened death.2.b. To explore patient perspectives on the clinical relevance of these measurable outcomes.

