Participant exclusion criteria include (i) cancer of, or metastasis to, the brain; (ii) symptoms consistent with delirium, psychosis, or other symptoms judged to be incompatible with establishment of rapport or safe exposure to psilocybin; (iii) history of past intolerability to psychedelics; (iv) past/present psychiatric diagnoses of bipolar disorder, psychotic disorder, active substance use disorder, or suicidality (as distinguished from desire for hastened death or readiness for death, per the discretion of the study team); (v) first degree relative with primary psychotic disorder if participant is under age 30; (vi) severe hypertension (SBP > 140 or DBP > 90) based on two readings on the same day; (vii) known paraneoplastic syndrome or “ectopic” hormone production by the primary tumor if incompatible with psilocybin, determined in consultation with the study palliative care physician; (viii) cardiovascular conditions including uncontrolled hypertension, angina, clinically significant ECG abnormality, transient ischemic attack in the last six months, stroke, peripheral or pulmonary vascular disease; (ix) uncontrolled epilepsy or history of seizures in the past 6 months; (x) gastrointestinal bleed in the past 6 months; (xi) participants with diabetes who are unable to skip a meal, require medication administration more than twice daily, or who have had symptomatic hypoglycemia within the prior 30 days; (xii) use of other investigational agents, psychoactive prescription medications (e.g., benzodiazepines, lithium, SSRIs), medications with primary pharmacological effect on 5-HT2A receptors (e.g., olanzapine), monoamine oxidase inhibitors, potent metabolic inducers (e.g., rifamycin, rifampin, rifabutin, rifapentine, carbamazepine, phenytoin, phenobarbital, nevirapine, efavirenz, paclitaxel, dexamethasone, St John’s wort), or inhibitors (e.g., HIV protease inhibitors, itraconazole, ketoconazole, erythromycin, clarithromycin, troleandomycin). In suitable patients, if safe to do so, contraindicated medications may be tapered prior to the start of the intervention.

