#### Safety (Objective 1.c)

Safety criteria are based on the number of participants experiencing no SAEs throughout the course of the trial. Green will be supported at 100%, amber at 85–100%, and red at or below 85%. Similar trials using psilocybin-assisted psychotherapy [18, 20] reported no SAEs. While we anticipate the same, we will allow for a slightly lower threshold given that our patient population may be more ill than the population recruited in previous studies.

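### Outside the dosing session, the stated recording of non-serious AEs is limited to events attributed to psilocybin after dosing, although the objective is the safety of PEARL therapy

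*Protocol article*

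**What the plan says.** All references are to the protocol article.

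- **Objectives, 1.c.** The aim is "To assess the safety of PEARL therapy". The object is the therapy, not the capsule alone.
- **Outcomes, Safety (AEs in general).** CTCAE version 5.0 is adopted for AE reporting. The recording rule follows: "AEs attributed to psilocybin will be monitored for and recorded after the psilocybin session".
- **Outcomes, Safety (during dosing).** The Monitor Rating Questionnaire "will be completed by therapists to capture AEs including elevated heart rate and blood pressure, confusion, headache, nausea/vomiting, anxiety, and paranoia". No attribution condition is attached. Heart rate and blood pressure are also measured on a fixed schedule.
- **Outcomes, Safety (SAEs).** "Serious adverse events (SAEs) will be tracked until study completion". The start of tracking is not given there.
- **Data analysis, Safety (Objective 1.c).** "Safety criteria are based on the number of participants experiencing no SAEs throughout the course of the trial". Non-serious AEs play no part in this criterion.
- **Participants, exclusion criteria.** "In suitable patients, if safe to do so, contraindicated medications may be tapered prior to the start of the intervention". Benzodiazepines, lithium and SSRIs are among the examples of excluded medicines.

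**The concern.** Relatedness is normally a judgement made about an event that has already been recorded. Here it is worded as a condition for recording. The trial is open-label and single-arm, in people with stage IV disease, so headache, nausea, anxiety or confusion in the days after dosing can readily be put down to the cancer or its treatment. An event so judged has no stated place in the AE record. Nobody can revisit the judgement later, and there is no control arm to show the background rate.

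The rule also points to the period after dosing. Half of the sessions come before it, and a taper may come earlier still, in participants selected for depressive symptoms. A participant who had non-serious worsening in that period and withdrew would appear in the adherence and retention figures, but with no AE under the stated rule.

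At stake is the non-serious AE profile that is meant to inform refinement of PEARL and the planned RCT.

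**Working it through.** The document states no AE rate or attribution rate, so there is no figure to reproduce. The check sets the stated capture routes against the course of the trial.

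**Session count** (PEARL intervention and its subsections): 3 initial + 1 preparatory + 1 psilocybin + 1 next-day integration + 2 follow-up = 8. Before dosing: 3 + 1 = 4 of 8.

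**Length of the pre-dose period.** The preparatory session is 1 week before dosing, integration is the day after, the two follow-ups are weekly, and the whole runs over 7 weeks. The spacing of the three initial sessions is not stated.
- If they are weekly (assumption), sessions fall on days 0, 7, 14, 21, 28 (dosing), 29, 36 and 43. Dosing comes 28 days, or 4 weeks, after the first session.
- If the full 7 weeks (49 days) are used, the part after dosing takes 1 + 7 + 7 = 15 days, which leaves 49 − 15 = 34 days before dosing.

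So roughly four to five of the seven weeks precede dosing, with any taper in addition.

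**Stated routes by period:**

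| Period | Non-serious AEs | SAEs |
|---|---|---|
| Taper, if any | none stated | tracked to study completion; start not stated |
| Four pre-dose sessions | none stated | as above |
| Dosing session (6–8 h) | questionnaire, no attribution condition | tracked |
| After the session, attributed to psilocybin | recorded | tracked |
| After the session, judged unrelated | none stated | tracked |

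**Does reading the timing words differently close the gap?** Suppose that the reference to the period after the session only says when the form is filled in. The attribution condition still applies, and an event before dosing cannot be attributed to a drug not yet taken. The pre-dose rows stay empty.

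**Direction of the effect.** In the post-session period, recorded incidence = true incidence × probability that staff attribute the event to psilocybin. The second factor cannot exceed 1, so the stated filter can only lower the count. How far below 1 it lies is unknown.

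**Effect on the progression criterion.** It is the share of 15 participants with no SAE: 15/15 = 100% is green, 14/15 = 93.3% and 13/15 = 86.7% are amber, and 12/15 = 80.0% is red. Non-serious AEs do not enter this share.

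**The case against.** The strongest reply is that the sentence is one of several provisions. The questionnaire covers the dosing session without an attribution filter and lists the very symptoms that are hardest to attribute. SAEs have separate tracking. CTCAE is adopted for AE reporting without limit, eCRF data are monitored for unexpected or adverse events, the T3 interview asks about negative effects of the intervention, and reasons for investigator withdrawal are documented. The article also condenses a fuller protocol that may set a wider AE window. Tapering is placed before the intervention, so its absence from the AE record does not by itself contradict Objective 1.c.

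Much of this stands, and it rules out stronger readings:

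- A reader might infer that nothing except psilocybin-attributed AEs is captured anywhere, or that the pre-dose period can yield no events at all. The questionnaire and the SAE route contradict the first. The second is not supported for serious events, since the criterion counts SAEs over the whole trial.
- A reader might put a percentage on the events lost. With no attribution rate in the document, any such figure only returns the share assumed.
- A reader might infer that the go/no-go safety result is biased. This sentence does not feed it. The SAE definition is tied to an adverse drug experience ("will be defined as any adverse drug experience that results in death, is life-threatening, requires hospital admission"), which fits poorly with a criterion covering the whole trial, but that is a separate question of wording.

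The reply does not fill the empty rows. CTCAE supplies terms and grades, not a rule on which events to enter. eCRF monitoring sees only what was entered. The interview is qualitative and takes place one month after PEARL completion. Nor is this a detail merely left to the full protocol: the article states a rule, and the rule is narrower than its objective.

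**Conclusion.** The point holds in a limited form. Outside the dosing session, the stated recording of non-serious AEs is restricted by prior attribution to psilocybin and by timing, while the objective covers a therapy with four of its eight sessions before dosing. Non-serious AEs before dosing, and later ones judged unrelated, have no stated route into the AE record.

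The consequence is a risk of downward bias in non-serious AE incidence and the loss of any chance to re-judge attribution. It is a risk and not a certainty, because the full protocol is not shown and may record more. Its size cannot be estimated from the document. The estimate of four to five pre-dose weeks assumes either weekly initial sessions or use of the full seven weeks; the count of four sessions does not depend on that. The sentence should be corrected, since events not recorded at the time cannot be reliably recovered, but it does not undermine the trial's progression decision.

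**What to change.** Replace the sentence with: *All AEs, regardless of attribution, will be recorded with CTCAE grade, onset date and relatedness (psilocybin / psychotherapy / medication taper / disease) from the earlier of taper start or first PEARL session through T4.* Tabulate all AEs and related AEs side by side, split before and after dosing. If the full protocol already works this way, it is enough to bring the published wording into line with it.

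The cost is additional eCRF entry for 15 participants, largely at contacts already scheduled. The tables will also be longer, with many events due to the underlying disease, so the text must explain that the all-AE column is not a count of drug effects.

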#### Additional data collection

The following demographic information will be collected via self-report: age, gender, sexual orientation, ethnicity, level of education, marital status, household income, and living arrangements. Medical and background information including cancer type and stage, length of illness, previous psychiatric and medical diagnoses, current medications, and past use of psychedelic medicines will be gathered via medical interview, physical examination, laboratory screening, and chart review. The Structured Clinical Interview for DSM Disorders (SCID) depression module will be administered to accurately assess for the current diagnosis of depression during screening.

### Data analysis

#### Feasibility (Objective 1.a)

Based on guidance for conducting feasibility trials [38, 39], we have established clear progression criteria (green/proceed, amber/amend, red/stop), informed by previous research on similar interventions in similar populations, to determine if the study findings indicate that it would be feasible to examine the efficacy of PEARL therapy in a larger RCT. All progression criteria will be summarized using descriptive statistics.

*Recruitment* criteria are based on the percentage of interested and eligible patients who consent to participate. Green (progression to RCT) will be supported at or above 40%, amber (minor protocol amendment before progression) at 10–40%, and red (significant protocol amendment before progression) at or below 10%. We are aiming for consent rates as high as Griffiths et al. [18] documented in their psilocybin-assisted psychotherapy trial among cancer patients (41%). Given that the PEARL protocol is more demanding and time-consuming for patients, we will allow for a slightly lower consent rate.

*Retention* criteria are based on the percentage of participants completing primary endpoint (T3) measures. Green will be supported at or above 75%, amber at 40–75%, and red at or below 40%. Criteria are based on 18–26% loss to follow-up rates in similar studies [11, 17, 18], and we will allow for loss on the higher end given the time commitment and demands of the PEARL protocol.

*Adherence* criteria are based on the percentage of participants completing all eight PEARL intervention sessions. Green will be supported at or above 70%, amber at 40–70%, and red at or below 40%. Criteria are based on the CALM RCT at PM, which achieved 77.5% adherence (completion of at least 3 sessions) among a similar target population [11]. We have chosen a lower threshold given that we are planning more sessions within a shorter time frame.

#### Acceptability (Objective 1.b)

Transcripts from qualitative interviews will be systematically coded using thematic analysis [40]. An initial set of themes regarding acceptability will be coded to form a tentative coding scheme. This scheme will be applied to new transcripts and revised to adjust for new information. Analysis will be conducted in an iterative process. An audit trail consisting of a detailed chronology of data collection and analytical decisions will be maintained, and regular team meetings will be conducted to discuss all phases of the analysis to resolve discrepancies and reach consensus.

#### Safety (Objective 1.c)

Safety criteria are based on the number of participants experiencing no SAEs throughout the course of the trial. Green will be supported at 100%, amber at 85–100%, and red at or below 85%. Similar trials using psilocybin-assisted psychotherapy [18, 20] reported no SAEs. While we anticipate the same, we will allow for a slightly lower threshold given that our patient population may be more ill than the population recruited in previous studies.

#### Efficacy outcomes (Objective 2.a)

The following outcome measures will be collected pre- and post-intervention at the time points indicated in the study calendar: death-related distress (Death and Dying Distress Scale (DADDS) [1, 14, 41]), depressive symptoms (Patient Health Questionnaire-9 (PHQ-9) [42]), anxiety symptoms (Generalized Anxiety Disorder scale (GAD-7) [43]), physical symptoms (Edmonton Symptom Assessment Scale (ESAS) [44]), demoralization symptoms (Demoralization Scale (DS) [45]), attachment style (the Experiences in Close Relationships Inventory (ECR) [46]), spiritual wellbeing (Functional Assessment of Chronic Illness Therapy-Spiritual Well-Being Scale (FACIT-Sp) [47]), quality of life (Quality of Life at the End of Life-Cancer Scale (QUAL-EC) [48]), attitudes toward hastened death (Schedule of Attitudes Toward Hastened Death (SAHD) [49]), and treatment expectancy (Stanford Expectation of Treatment Scale (SETS) [50]). Outcome measure packages will take an average of 25 min to complete. In our previous intervention studies in this population, measure packages of similar length were found acceptable to participants.

The following measures will only be completed post-dosing session to capture phenomena related to the psilocybin experience: quality of acute drug experience (Mystical Experience Questionnaire (MEQ30) [51]), persisting effects (three questions from the Persisting Effect Questionnaire (PEQ) [52]: (1) how personally meaningful was the experience, (2) how spiritually significant was the experience, and (3) did the experience change your sense of well-being or life satisfaction and emotional breakthrough (Emotional Breakthrough Inventory (EBI) [53]).

As a feasibility study, we consider all efficacy analyses to be exploratory and therefore will not be interpreting or disseminating the study outcome results as definitive and will not rely on any imputation methods. Outcome measures will be summarized with descriptive statistics, and dependent *t*-tests will be used to examine change over time, comparing each endpoint assessment to baseline with an intention-to-treat (ITT) analysis.

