#### Discontinuation criteria

Participants can withdraw from treatment or withdraw from the study at any time for any reason. The investigator may withdraw a participant if (a) the participant develops any conditions listed within the exclusion criteria (e.g., medical or psychiatric diagnosis/symptoms) that affect the safety of the participant, (b) the participant cannot comply with elements of the protocol that are critical for safety, or (c) in their clinical judgment, it is in the best interest of the participant. If the clinical team decides to terminate a participant from the study, they will explain to the participant, document the reason for removal, and ensure the participant has an appropriate follow-up support plan.

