### Study procedures

The study schedule is organized as follows (see Fig. 1). Potentially eligible participants will be referred from outpatient clinics at PM. Research staff will contact potential participants to obtain consent for initial screening, which involves medical chart review, laboratory investigations, and psychiatric assessment. Participants assessed as potentially eligible will continue to the final screening procedures once informed consent for the main study is obtained. If participants meet all inclusion/exclusion criteria, they will be enrolled in the trial and complete baseline questionnaires (T0) within 1 week. Participants will begin the PEARL intervention within 1 to 2 weeks of T0. On the day following the psilocybin session, participants will complete questionnaires to assess the quality of the experience (T1). Participants will complete follow-up questionnaires 2 weeks (T2) following PEARL completion, a qualitative interview 1 month following PEARL completion (T3), and follow-up questionnaires 3 months following PEARL completion (T4). The assessments, intervention components, and questionnaires completed at each time point are outlined in the study calendar (Fig. 2).

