### Sample size

We have chosen a target sample size of 15 participants. There is little consensus in the literature regarding sample sizes required for single-arm feasibility and acceptability studies, and guidance varies depending on study design and goals, as well as pragmatic issues such as the value of information, study cost, and other constraints [34]. In terms of human resources, time, and the price of psilocybin (a controlled substance that is expensive to purchase and import into Canada), this is a costly complex intervention to deliver, and therefore, the smallest meaningful sample size was preferred. The likely sample size of any future definitive RCT also informed our decision. While this is not a pilot RCT, it has been suggested that the size of a pilot trial should be informed by the size of the future definitive RCT with possible sample sizes of 10 to 75 depending on the potential effect size (from large to very small) [35]. Given the large effect sizes reported following previous psilocybin-assisted psychotherapy RCTs in this population (treatment arms in these trials ranged from 16 [20] to 29 [18]), a sample size of 15 for this single-arm study was deemed reasonable. Finally, our primary objectives include examination of both quantitative and qualitative indicators of feasibility and acceptability. Considering quantitative indicators, with a sample size of 15, we will be able to estimate, with 95% confidence, the anticipated recruitment rate of 40% with 25% absolute precision and the anticipated retention rate of 75% with 20% absolute precision. Considering qualitative indicators, samples of less than 20 have been deemed suitable for qualitative feasibility research [36].

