#### Data management and trial oversight

All data obtained in the clinical trial will be reported on electronic case report forms (eCRFs). All data will be source verified prior to publication; the investigator will review the data and electronically sign the eCRFs to acknowledge agreement with the data entered.

Data collected from all enrolled participants will be included in the analysis. If a participant withdraws or is terminated from the study, data collected up to that point will be included in analyses unless the participant specifically requests their data not be included. Any planned or unplanned deviation(s) from the original statistical plan will be described in the final report. Study termination and follow-up will be performed in compliance with the conditions set forth in the International Conference on Harmonisation (ICH) sixth efficacy publication on Good Clinical Practice. As per Health Canada regulations, all original records will be maintained for 15 years after study completion.

A trial steering committee composed of the principal investigators and external experts in clinical trials will provide oversight of study progress and procedures, ensure adherence to protocols and standards, and advise on ethical issues. Data safety monitoring will be performed by the PM Drug Development Program Central Office. Trial data in eCRFs will be monitored on an ongoing basis for unexpected or adverse events, and quality assurance measures will be performed.

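### The analysis labelled intention-to-treat is an available-case analysis, and dating T2 to T4 from PEARL completion leaves early stoppers without a follow-up date

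*Protocol article*

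**What the plan says.** **Analysis.** Under Efficacy outcomes (Objective 2.a), the protocol article states that dependent t-"tests will be used to examine change over time", "comparing each endpoint assessment to baseline with an intention-to-treat (ITT) analysis". The same paragraph says that the study "will not rely on any imputation methods" and that "we consider all efficacy analyses to be exploratory". Data management and trial oversight adds: "Data collected from all enrolled participants will be included in the analysis". For a participant who withdraws or is removed, data gathered by then are kept unless the participant objects.

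**Visits.** Study procedures places the T2 questionnaires 2 weeks after PEARL completion, followed by "a qualitative interview 1 month following PEARL completion (T3), and follow-up questionnaires 3 months following PEARL completion (T4"). Discontinuation criteria distinguishes withdrawal from treatment from withdrawal from the study. Removal by the team is worded as removal from the study: "If the clinical team decides to terminate a participant from the study".

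**Size.** "We have chosen a target sample size of 15 participants". The feasibility criteria cite 18–26% loss to follow-up in similar studies. Retention is scored at T3 (green at 75% or more). Adherence is the share completing all eight sessions (green at 70% or more).

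**The concern.** Two statements do not fit together. Intention-to-treat means that everyone enrolled is represented in the comparison. A paired t-test with no imputation represents only those with a baseline score and a score at the visit in question. A reader of the results would credit the analysis with a property that it lacks.

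The visit definition adds to this. A participant may stop PEARL and remain in the study, but the text then gives no event from which to count T2, T3 or T4. If no assessment is scheduled, data go missing because treatment stopped, and in stage IV cancer treatment may stop because of intolerance or decline.

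Three things are at stake:
- the mean changes reported to inform a later RCT;
- the T3 retention figure, which is a progression criterion;
- whose views on acceptability are heard, since T3 is the interview.

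**Working it through.** The article gives no expected number of pairs and no power figure for the t-tests, so there is no stated efficacy figure to reproduce.

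**1. Pairs per test.** Inputs: n = 15 (Sample size); loss 18–26% (Feasibility).
- 15 × (1 − 0.18) = 12.3
- 15 × (1 − 0.26) = 11.1

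So about 11 or 12 pairs, with 3 or 4 missing. The anticipated 75% retention gives 0.75 × 15 = 11.25, but that rate refers to T3, the interview visit, and only indicates what T2 or T4 might yield.

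**2. What the missing participants could change.** Let k be observed with mean change Δ, and let the other 15 − k have mean change m. The mean over all enrolled is [kΔ + (15 − k)m] / 15. Δ = 5 points and every m below are assumptions.

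| Mean change in the missing | All 15, k = 11 | Observed mean exceeds it by | All 15, k = 12 | Observed mean exceeds it by |
|---|---|---|---|---|
| 5 (same as observed) | 5.00 | 0% | 5.00 | 0% |
| 2.5 | 4.33 | 15% | 4.50 | 11% |
| 0 | 3.67 | 36% | 4.00 | 25% |
| −2.5 | 3.00 | 67% | 3.50 | 43% |

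Example: (11 × 5 + 4 × 0) / 15 = 3.67, and 5 / 3.67 = 1.36.

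**3. Effect on the test.** Simulation of 15 participants with 75% observed on average, SD of change 1 and true change 0. The link between improving and being observed (log-odds per SD of improvement) is assumed.

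| Log-odds | Mean observed change (SD) | Chance of p < 0.05 |
|---|---|---|
| −1 | −0.21 | 10.5% |
| 0 | 0.00 | 4.8% |
| 0.5 | 0.12 | 6.7% |
| 1.0 | 0.21 | 10.4% |
| 1.5 | 0.28 | 15.0% |

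The sign of the bias follows the sign of an assumption that the documents do not settle.

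**4. Timing.** T4 falls about 21 to 22 weeks after T0: 1–2 weeks to start, 7 weeks of PEARL, and about 13 weeks more. Eligibility requires expected survival above 6 months, so loss through illness or death before T4 is plausible but not established.

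**5. Visit anchor and the progression criteria.** Suppose 11 of 15 complete all eight sessions: 11/15 = 73.3%, so adherence is green. Suppose also that the other 4 stopped early and have no T3 because none is dated. Retention is then 73.3%, which is amber. If one of the 4 were seen at T3, it would be 12/15 = 80%, which is green. The anchor alone could move this signal.

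**6. Would a mixed model help?** With a baseline score for all and a follow-up score for some, the likelihood estimate of mean change is the observed mean change minus (1 − β)D. Here β is the slope of follow-up on baseline, and D is the baseline mean of all minus that of the observed. If those lost had similar baselines, D is near 0 and the estimate stays near 5.0. A simulation of the 11-and-4 example gave 4.98 for the paired test and 4.99 for a random-intercept model, against 3.67 in truth.

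**The case against.** The strongest reply is that this is a loose label on an exploratory, secondary objective in a 15-patient study. Efficacy results are not to be presented as definitive, and the progression criteria cover recruitment, retention, adherence and safety only. Declining imputation at this size is reasonable. All of that stands and limits the harm.

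Several stronger readings are tempting, and the documents do not support them:
- **A completer analysis.** Nothing excludes a participant who stops treatment but still answers questionnaires.
- **Loss of all data from anyone who misses T4.** Each endpoint is compared with baseline separately, so someone with T0 and T2 stays in the T2 test, and all scores enter the descriptive summaries. The promise to include all enrolled participants' data can be read as met in that sense.
- **A result that drops the sickest and flatters the change.** The Discussion says only that a vulnerable population may make retention and adherence difficult. It gives no direction of bias.
- **Four participants without follow-up dates at the adherence threshold.** Missing one of eight sessions is not stopping early; someone who attends the last session still has an end date.
- **Interviews restricted to completers.** The Acceptability section sets no such limit; the difficulty arises only from how T3 is dated.

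Finally, the study schedule and calendar figures are not shown, and a full protocol may define visits further. That lowers confidence in the second part. It does not remove it, because the text does fix an anchor, and that anchor does not exist for early stoppers. The exploratory status does not rescue the label either: it limits interpretation but does not make observed pairs intention-to-treat.

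**Conclusion.** The point holds in two parts. First, the efficacy tests are available-case, on about 11 or 12 of 15 participants if the cited loss rates apply, and should not be called intention-to-treat. Second, the text gives no T2, T3 or T4 date to a participant who stops PEARL but remains in the study, which can make missingness depend on tolerability or deterioration and reaches primary objectives through T3.

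The size of any bias is unknown. It is zero if missingness is unrelated to change, 36% in the 11-and-4 illustration, and could run the other way. A reader might infer a proven overstatement of benefit; the documents do not support that. The practical harm to efficacy is limited by its exploratory status. The visit anchor matters more, because assessments that are never collected cannot be recovered.

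**What to change.** 1. **Label and reporting.** Call the t-tests an available-case analysis of enrolled participants. At each visit report the mean change with its 95% CI, the number of pairs, and the reasons for missing scores (death, deterioration, withdrawal). A mixed model on all observed scores is an optional addition. It is valid only under missing-at-random and does not correct for participants who have a baseline only.
2. **Visit dating.** For those who stop early, date T2–T4 from the scheduled end of PEARL or from T0. State that questionnaires continue, and that the T3 interview is offered, after withdrawal from treatment unless consent is withdrawn. Serious adverse events are already tracked to study completion, so nothing is needed there. This concerns data collection only and changes no rule for stopping treatment.

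Cost: a few sentences, a few extra questionnaires and interviews, and a less favourable label.
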